### 4 Study design, population, and eligibility

#### 4.1 Design

This is a prospective cohort study to develop new diagnostic biomarkers for isolated spinal TB versus disseminated spinal TB and treatment monitoring. Furthermore, this study investigates genetic variability of *Mtb.* in spinal TB and its distributional pattern. After MRI-confirmation of spinal TB according to local algorithms, patients will be invited to join the study. At baseline, clinical examination as well as blood biobanking will be performed. Every patient with unknown HIV status will undergo HIV-testing. Sputum will be collected for *Mtb.* culture and GeneXpert as well as specimens from other sites of TB diseases (e.g. urine, FNA) and screening for diabetes and pregnancy will be performed. Whole-body PET/CTs will be performed at time of diagnosis (0 month), 6 months, and 12 months of treatment. Either spinal biopsies or surgery will be performed according to clinical indication to confirm the diagnosis of spinal TB at baseline after imaging modalities have been performed (MRI and PET/CT).

## 4.2 Participant characteristics

Participants with clinically and MR-suspected spinal TB will be recruited from Groote Schuur Hospital, Cape Town, South Africa, its affiliated hospitals, UCT Private Academic Hospital and other private hospitals in the region. According to the current caseload, we will be able to include 50 participants per year, aiming for 100 participants in total. However, if recruitment goals cannot be achieved according to aim, Tygerberg Hospital, Cape Town, South Africa may be approached to enhance recruitment. In result, we are aiming for 300 PET/CTs (100 initial, 100 at 6 months, 100 at 12 months) and 300 peripheral blood samples for gene expression analysis.

### Spinal TB X - Study Flow

[figure not shown]

## 4.3 Eligibility Criteria

### Inclusion Criteria

1. Participant has completed the written informed consent process prior to undergoing any clinical evaluations and willing to undergo HIV testing
2. TB spine based on clinical and radiological criteria
3. Age 18 or older with a body weight of at least 40 kg body weight
4. Able and willing to return to follow-up
5. Willing to have samples, including DNA including RNA extraction, stored
6. Willing to consistently practice a highly reliable method of pregnancy prevention

### Exclusion Criteria

1. Pregnancy or active desire to become pregnant within the next 6 months.
2. Uncontrolled diabetes (HbA1c  $\geq 6.5\%$  / random glucose concentration  $\geq 11.1$  mmol/l, fasting plasma glucose  $\geq 7.0$  mmol/l)
3. Alcohol and substance abuse which might interfere with medication adherence during the trial
4. Positive SARS-CoV-2 PCR in the past 4 weeks
5. Suspicion of malignancy on MRI or known malignancy
6. Suspicion of inflammatory disease and other rheumatological conditions

7. Any person for whom the physician feels this study is not appropriate
8. Age under 18 years

#### 4.4 Ethical approval

The trial will adhere to International Conference on Harmonisation Good Clinical Practice (ICH/GCP) guidelines, and approval will be requested from the University of Cape Town's Faculty of Health Sciences Human Research Ethics Committee (UCT HREC).

### 5 Study Schedule and Study Timelines

Spinal TB X - study timelines

| Visit                                               | SCR   | PET1   | POST-PET | Surgery/CT guided biopsy | M 1 to 5 | PET 2    | M 7 to 11 | PET 3     |
|-----------------------------------------------------|-------|--------|----------|--------------------------|----------|----------|-----------|-----------|
| Time point in relation to SCR                       |       | 1 week | 2 weeks  | by indication            | monthly  | 6 months | monthly   | 12 months |
| Visit window (in days)                              | N/A   | +/- 10 | +/- 10   | N/A                      | +/-10    | +/-10    | +/-10     | +/-10     |
| Study informed consent plus HIV test consent        | X     |        |          |                          |          |          |           |           |
| Study arm                                           |       |        |          |                          |          |          |           |           |
| Vital signs                                         | X     | X      | X        |                          |          | X        |           | X         |
| Medical history                                     | X     | X      | X        |                          | X        | X        | X         | X         |
| Co-medication                                       | X     | X      | X        |                          | X        | X        | X         | X         |
| Physical examination (including neurology)          | X     | X      | X        |                          |          | X        |           | X         |
| TB specimen collection                              |       |        |          |                          |          |          |           |           |
| Sputum - TB culture (MGIT)              | X     |        |          |                          |          |          |           |           |
| Sputum - GeneXpert Ultra                            | X     |        |          |                          |          |          |           |           |
| Urine- TB culture (MGIT)                | X     |        |          |                          |          |          |           |           |
| Urine - GeneXpert Ultra                             | X     |        |          |                          |          |          |           |           |
| Site(s) of disease - TB culture (MGIT)  |       |        | X        |                          |          |          |           |           |
| Site(s) of disease - GeneXpert Ultra                |       |        | X        |                          |          |          |           |           |
| Spinal biopsy - TB culture (MGIT)       |       |        |          | X                        |          |          |           |           |
| Spinal biopsy - GeneXpert Ultra                     |       |        |          | X                        |          |          |           |           |
| Blood collection                                    |       |        |          |                          |          |          |           |           |
| Serum chemistry                         | X     |        |          |                          |          | X        |           | X         |
| Full blood count                                    | X     |        |          |                          |          | X        |           | X         |
| HBA1C                                               | X     |        |          |                          |          |          |           |           |
| HIV-1 testing                           | X     |        |          |                          |          |          |           |           |
| CD4+ count                              | X     |        |          |                          |          |          |           |           |
| HIV-1 viral load                        | X     |        |          |                          |          |          |           |           |
| Blood biomarkers (PaxGene, Heparin, Serum)          |       | X      |          |                          |          | X        |           | X         |
| Max. blood volume per visit                         | 50 ml | 50 ml  |          |                          |          | 50 ml    |           | 50 ml     |
| Finger prick                                        |       |        |          |                          |          |          |           |           |
| Glucose                                             | X     | X      |          |                          |          | X        |           | X         |
| Urine collection                                    |       |        |          |                          |          |          |           |           |
| Urine beta-HCG                          | X     | X      |          |                          |          | X        |           | X         |
| Imaging                                             |       |        |          |                          |          |          |           |           |
| FDG PET/CT                                          |       | PET1   |          |                          |          | PET2     |           | PET3      |
| Follow-up                                           |       |        |          |                          |          |          |           |           |
| Telephonic follow-up                                |       |        |          |                          | X        |          | X         |           |
| Adherence monitoring                    |       |        |          |                          | X        | X        | X         | X         |

Storage of MTB culture colonies at laboratory

ALT, creatinine, hsCRP

For all participants not on ARVs

For participants tested positive for HIV or on ARVs

Women only

TB drug adherence questionnaire

Version 1.0 10 Dec 2021

#### 5.1 Participant Screening (SCR)

Participants with a confirmed diagnosis of spinal TB based on clinical presentation and MRI will be enrolled. participants who sign the **Main Informed Consent Form and HIV-Testing Consent Form** will undergo screening. The following will then be performed/obtained:

1. Vital Signs
2. Medical history and co-medications
3. Physical examination (including neurology)
4. Induced sputum samples (total sputum volume at least 3 mL) for TB culture (MGIT) and GeneXpert Ultra (Xpert).
5. Urine sample for TB culture (MGIT) and GeneXpert Ultra (Xpert)
6. Blood draw for (fasting prior to phlebotomy, max. 50 mL):
  1. Full blood count (including differential), serum chemistry (ALT, creatinine, hsCRP)

2. Diabetes screening (HbA1c)
3. HIV-1 ELISA testing, for all patients not on ART
4. CD4 count and HIV-1 viral load, for all participants tested positive for HIV or on ART
7. Finger prick for random glucose testing
8. Urine collection for pregnancy testing (beta-HCG)

Note that at this and all subsequent visits, if a sputum culture or blood sample is found to be contaminated or is otherwise unevaluable, the participant may be called back to provide another sputum sample. If for some reason a participant needs to come back the next day to provide sputum, this will not be a deviation. In addition, it will not be a protocol deviation if a participant is unable to provide sufficient sputa to perform all sputum-related testing at any study visit.

## **5.2 PET/CT imaging 1**

If eligibility is given, participants will undergo PET/CT imaging within 10 (+/- 10 days) days of screening visit (SCR). The following will then be performed/obtained at this visit:

1. Vital signs
2. Medical history and co-medications
3. Physical examination (including neurology)
4. Blood draw for biomarkers (PaxGene, Heparin, Serum)
5. Finger prick for random glucose testing
6. Urinary bladder catheterization in participants who are (potentially) incontinent
7. Urine collection for pregnancy testing (beta-HCG)
8. PET/CT imaging (pregnancy test is negative)

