## **5.6 PET/CT imaging 2**

6 months after the first PET/CT, participants will undergo second PET/CT imaging (+/- 10 days). The following will then be performed/obtained at this visit:

1. Vital Signs

2. Medical history and co-medications
3. Physical examination (including neurology)
4. Blood draw for (fasting prior to phlebotomy, max. 50 mL): full blood count (including differential), serum chemistry (ALT, creatinine, hsCRP)
5. Blood draw for biomarkers (PaxGene, Heparin, Serum)
6. Finger prick for random glucose testing
7. Urinary bladder catheterization in participants who are (potentially) incontinent
8. Urine collection for pregnancy testing (beta-HCG)
9. PET/CT imaging (pregnancy test is negative)
10. Adherence monitoring

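### A same-day full blood count with differential is not guaranteed for the baseline mRNA sample, although it is scheduled with the mRNA sample at 6 and 12 months

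*Protocol*

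**What the plan says.** **Baseline.** Section 5.1 places the count at screening: "Full blood count (including differential), serum chemistry (ALT, creatinine, hsCRP". Section 5.2 places the RNA sample at the first scan visit: "Blood draw for biomarkers (PaxGene, Heparin, Serum". The 5.2 list contains neither a full blood count nor serum chemistry.

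**Follow-up.** Section 5.6 asks for "Blood draw for (fasting prior to phlebotomy, max. 50 mL): full blood count (including differential), serum chemistry (ALT, creatinine, hsCRP" and, at the same visit, the PAXgene draw and the scan. Section 5.8 does the same at 12 months.

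**Schedule table (section 5).** The row "Full blood count" is marked at SCR, PET2 and PET3 and is blank at PET1. The row "Blood biomarkers (PaxGene, Heparin, Serum" is marked at PET1, PET2 and PET3 and is blank at SCR. Table and text agree on this allocation.

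**Gap between SCR and PET1.** Section 5.2 states that "participants will undergo PET/CT imaging within 10 (+/- 10 days) days of screening visit (SCR". The table, in the row "Time point in relation to SCR", gives 1 week for PET1 with a visit window of +/- 10 days.

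**Use of the sample.** The primary objective (section 3) includes the mRNA profiles of isolated versus disseminated spinal TB, stratified by HIV status. Section 6.5 lists PAXgene draws at baseline, 6 months and 12 months.

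**The concern.** Expression measured in whole blood depends in part on the proportions of neutrophils, lymphocytes and monocytes in the tube. Extent of disease and HIV status could each plausibly shift those proportions. When a gene set separates isolated from disseminated disease, one of the first questions is whether it says more than the differential count already does. The cleanest answer uses a differential from the same draw.

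The protocol schedules that pairing at both follow-up visits but not at baseline, which is the natural time point for the primary comparison. An analysis plan can specify an adjustment or a sensitivity analysis, but it cannot create a count that was not taken. So this belongs to the visit schedule, and a statistical analysis plan that is not shown could not settle it.

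**Working it through.** **1. Visit allocation (section 5 table; sections 5.1, 5.2, 5.6, 5.8).**

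| Time point | Count with differential | PAXgene | PET/CT | Same visit? |
|---|---|---|---|---|
| Baseline | SCR | PET1 | PET1 | No |
| 6 months | PET2 | PET2 | PET2 | Yes |
| 12 months | PET3 | PET3 | PET3 | Yes |

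**2. Lag between the baseline count and the RNA sample.**
- Section 5.2, read as 10 +/- 10 days: 10 - 10 = 0 to 10 + 10 = 20 days.
- Table, 7 +/- 10 days: 7 - 10 = -3 to 7 + 10 = 17 days. PET1 follows screening, so in practice 0 to 17 days.

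The nominal lag is 10 days or 7 days, depending on which place is followed. Both windows allow the same day.

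**3. Could another PET1 sample supply the differential?** By section 6.5 the heparin tube is for PBMC isolation, the SST tube is for serum mediators, and the PAXgene tubes are for mRNA. None is planned to yield a differential. Section 6.5 permits repeat testing for abnormal results; it does not make a count at PET1 routine.

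**4. Blood volume at PET1 (maxima in section 6.5).**
- As listed: SST 4 + heparin 36 + PAXgene 5 = 45 mL.
- With a full blood count: 45 + 4 = 49 mL, against the table's 50 mL per visit.
- With a separate 5 mL chemistry tube as well: 49 + 5 = 54 mL, above the maximum.

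**5. What a lagged count could leave unadjusted (illustration only).** Assume that the whole group difference in expression comes from cell mix, that the group shift D in the count is the same at both dates with equal variance, and that the SCR and PET1 counts correlate at r within group. With effect b of the count on expression, the unadjusted difference is bD. Adjusting for the SCR count uses slope br and removes brD, which leaves bD(1 - r).

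| Assumed r | Share left, 1 - r | Simulated remainder (bD = 0.5) |
|---|---|---|
| 0.5 | 50% | 0.249 |
| 0.7 | 30% | 0.15 |
| 0.9 | 10% | 0.05 |
| 1.0 (same-day count) | 0% | 0.0 |

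The protocol gives no value of r. The table only restates the assumed correlation and does not estimate the loss in this study.

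**The case against.** **The schedule is internally consistent, and a baseline differential exists.** This is true. A reader might infer that baseline has no concurrent cell-count covariate at all. The protocol does not support that: a differential is taken at SCR, and both windows allow PET1 on the same day. What is missing is the guarantee.

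**No cell-count-adjusted mRNA analysis is stated.** Section 6.13 says only that laboratory findings will be analysed. The stated aim is diagnostic, and a signature that carries a shift in white cells can still discriminate. This stands against calling the schedule an error. It does not remove the value of knowing whether a costly RNA signature adds anything to a routine differential. Cell mix can also be estimated from the expression data, but that is an indirect substitute.

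**Changes from baseline.** A reader might also infer that changes from baseline mix two sampling dates. They do not: each marker has a single baseline date. A mismatch would arise only if change in counts or hsCRP were set beside change in mRNA or PET values, and the protocol states no such analysis.

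**Baseline as the primary time point is inferred.** The primary objective names no time point, and the title covers diagnosis, 6 and 12 months. Baseline is the natural reading for a diagnostic comparison, but it remains a reading.

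**Nothing shows that counts would move materially in the gap.** This is also correct. The protocol does not fix the start of TB treatment relative to SCR and PET1, so stability over the gap is unknown in either direction.

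**Conclusion.** The point holds as a cheap improvement to the sampling schedule; it is not a contradiction or a flaw that invalidates the plan. At baseline the differential may precede the PAXgene sample by up to 20 days (section 5.2) or 17 days (table), whereas at 6 and 12 months both are drawn at one visit. The check for a signature driven by white-cell mix is therefore weaker at baseline than at follow-up. How much weaker cannot be stated from the protocol: under the assumptions shown, the unremoved share is 1 minus the correlation between the two counts, and that correlation is not given. The conclusion rests on two premises: that whole-blood expression partly reflects cell mix, and that baseline is where isolated and disseminated disease will mainly be compared.

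**What to change.** Keep the count at SCR. Add a full blood count with differential (4 mL EDTA) to the PET1 column of the schedule table and to the section 5.2 list, drawn with the PAXgene tubes. State that this is the baseline count for the mRNA analysis.

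Reconcile the SCR-to-PET1 window, which is 10 +/- 10 days in section 5.2 and 1 week +/- 10 days in the table.

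Cost: one extra count per participant, about 100 in all, with no added visit or needle. The listed PET1 tubes rise from 45 to 49 mL, which leaves 1 mL under the 50 mL maximum.

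Two apparent shortcuts are not recommended. Moving the count away from SCR would remove information that may inform the exclusions for suspected inflammatory disease and physician judgement. Running baseline hsCRP on the PET1 SST serum would compete with the cytokine and mediator assays and could differ in handling from the chemistry tube used at follow-up.

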## **5.3 Post PET/CT**

After PET/CT imaging (within 10 days after PET/CT, +/- 10 days), the following will be performed/obtained at this visit:

1. Vital Signs
2. Medical history and co-medications
3. Physical examination (including neurology)
4. Samples of site(s) of disease (according to PET/CT) if accessible conservatively for TB culture (MGIT) and GeneXpert Ultra (Xpert).

## **5.4 Surgery**

Surgery will be performed by the Department of Orthopaedics if indication is given. Should surgery be performed, spinal biopsies will be obtained for TB culture (MGIT) and GeneXpert Ultra (Xpert).

## **5.5 Month 1 to Month 5**

Between the first and the fifth month, adherence monitoring as well as obtaining participant's medical history and co-medication will be performed via monthly telephonic follow-ups.

## **5.6 PET/CT imaging 2**

6 months after the first PET/CT, participants will undergo second PET/CT imaging (+/- 10 days). The following will then be performed/obtained at this visit:

1. Vital Signs

2. Medical history and co-medications
3. Physical examination (including neurology)
4. Blood draw for (fasting prior to phlebotomy, max. 50 mL): full blood count (including differential), serum chemistry (ALT, creatinine, hsCRP)
5. Blood draw for biomarkers (PaxGene, Heparin, Serum)
6. Finger prick for random glucose testing
7. Urinary bladder catheterization in participants who are (potentially) incontinent
8. Urine collection for pregnancy testing (beta-HCG)
9. PET/CT imaging (pregnancy test is negative)
10. Adherence monitoring

### **5.7 Month 7 to Month 11**

Between the seventh and the eleventh month, adherence monitoring as well as obtaining participant's medical history and co-medication will be performed via monthly telephonic follow-ups.

### **5.8 PET/CT imaging 3**

12 months after the first PET/CT, participants will undergo third PET/CT imaging (+/- 10 days). The following will then be performed/obtained at this visit:

1. Vital Signs
2. Medical history and co-medications
3. Physical examination (including neurology)
4. Blood draw for (fasting prior to phlebotomy, max. 50 mL): full blood count (including differential), serum chemistry (ALT, creatinine, hsCRP)
5. Blood draw for biomarkers (PaxGene, Heparin, Serum)
6. Finger prick for random glucose testing
7. Urinary bladder catheterization in participants who are (potentially) incontinent
8. Urine collection for pregnancy testing (beta-HCG)
9. PET/CT imaging (pregnancy test is negative)
10. Adherence monitoring

## **6 Detailed description of study procedures**

### **6.1 Informed consent**

Informed consent is a process where information is presented to enable persons to voluntarily decide whether to participate as a research participant. It is an ongoing conversation between the participant and the researchers, which begins before consent is given and continues until the end of the participant's involvement in the research. Discussions about the research will provide essential information about the study and include purpose, duration, procedures, alternatives, risks, and benefits. Participants will be given the opportunity to ask questions and have them answered.

There will be a **Main Informed Consent Form and HIV-Testing Consent Form**. If the person is potentially eligible and interested in joining the trial, the Main Consent Form and HIV-Testing Consent Form will be used at the participant's screening visit and before any study related procedures are performed. The informed consent process for both Consent Forms will be conducted by research staff such as clinical research workers, nurses, study coordinators, doctors, or other qualified investigators. The person obtaining informed consent will ask questions to assess the participant's understanding of

the mentioned Consent Forms and state that participation is voluntary and that participants may refuse participation or withdraw at any time without prejudice to their clinical care.

The consent forms will be prepared in English and translated to Xhosa and Afrikaans.

The participant will sign the informed consent documents prior to undergoing any procedures. The researcher will also sign the ICF and document the consent process in the participant's research and/or medical record. Participants will also be informed that study results will be made available to them in the future by means of pamphlets, leaflets, phone calls, SMS or radio broadcasting. Consent forms will be stored securely at study sites as per GCP requirements.

